### Usual care

The usual care will include the usual stroke care services available to the participants during the study period. It will include, but not be limited to, medical consultations or rehabilitation services offered by the hospital or health organisations.

### Quantitative outcome measures

#### Primary outcome

##### Community reintegration

The Chinese version of the Reintegration to Normal Living Index (RNIL-C) will be used to assess the participants’ level of community reintegration [26, 27]. It consists of 11 items in eight domains: mobility, self-care, daily work and school activity, recreational and social activities, family roles, personal relationships, presentation of self to others and general coping skills. Participants will be asked to rate the extent to which each item describes their situation on a scale from 1 – ‘a small extent’ to 5 – ‘a great extent’. The total score is calculated by summation and normalised to give 100 with a total score range of 25 to 100. A higher score indicates better community reintegration. The RNIL-C has high internal consistency (Cronbach’s alpha = 0.92) and good convergent validity [27].

#### Secondary outcomes

##### Depressive symptoms

The Chinese version of the 15-item Geriatric Depression Scale will be used to measure participants’ depressive symptoms [28, 29]. Studies support its utility in younger adults (> 18 years old), with good diagnostic sensitivity and specificity [30, 31]. Each item represents symptoms of depression and describes a participant’s condition in the preceding week; the participants answer each item with either ‘yes’ or ‘no’. All items are summed (total score 0–15). A score of six or greater is a cutoff for depression. The scale has a Cronbach’s alpha of 0.78 [29].

##### HRQoL

Participants’ HRQoL will be measured by the Chinese version of the Stroke-Specific Quality of Life Scale [32, 33], which has 47 items with 11 domains ranging from physical to psychosocial and participation. The items are about the health conditions of the participants and how much difficulty the participants have when doing everyday self-care tasks. The items are scored from 1 – ‘strongly disagree/cannot do it’ to 5 – ‘strongly agree/no trouble’. Total score is yielded by summing all item scores (range 47–235): the higher the score, the higher the HRQoL. It has acceptable internal consistency (Cronbach’s alpha: 0.63–0.93) and convergent validity [33].

##### Self-management behaviours

The 11-item Chinese version of the Stroke Self-management Behaviours Performance Scale will be adopted to assess participants’ satisfaction with the performance of self-management behaviours. Each item is scored using a range from 0 – ‘very dissatisfied’ to 10 – ‘very satisfied’. Taking the sum of all item scores yields one total score (range 0–110), and the higher the score, the higher the satisfaction. This scale has a Cronbach’s alpha of 0.93 [23].

##### Self-efficacy

The Chinese version of the Stroke Self-Efficacy Questionnaire will be used to measure self-efficacy [34, 35]. It has 13 items, each is scored using a scale from 0 – ‘no confidence’ to 10 – ‘very confident’. The items are about the participants’ perceived extent of confidence in doing everyday activities and self-management tasks. A total score is yielded by summing all items (range 0–130). A higher total score represents higher self-efficacy. The scale has acceptable internal consistency (Cronbach’s alpha = 0.92) and convergent validity [35].

##### Outcome expectation

The Chinese version of the Stroke Self-management Outcome Expectation Scale will be used to measure the participants’ outcome expectation beliefs. It has 11 items, each rated using a scale from 0 – ‘strongly disagree’ to 10 – ‘strongly agree’. The score of each item indicates the participants’ confidence in the expected outcomes to occur. All item scores will be calculated by summation (total score 0–110). A higher score represents higher outcome expectations. This scale has good internal consistency (Cronbach’s alpha = 0.94) [23].

### Qualitative evaluation

Focus group interviews with participants who received the NSI will be conducted at a community centre immediately and 12 months post-intervention. A convenience sample of 56 participants (7 per group) will be invited. The participants will be asked to share their experience and satisfaction with the NSI, views on usefulness of the NSI in initiating and supporting their engagement in valued everyday activities, family and social roles, met and unmet health needs, and areas for enhancement. The facilitator who delivered the NSI will also be interviewed using a semi-structured interview guide immediately after the completion of the intervention to elicit feedback on the facilitators of and barriers to implementation of the NSI.

### Demographic and clinical information

Data will be recorded on the participants’ age, gender, educational level, marital status, occupation, current financial aids received, type of housing, living condition, past and present medical history, and assistive aids used. Scales such as the MoCA, the Barthel Activities Daily Living Index, mRS and the National Institutes of Health Stroke Scale will be administered. Information about the locations of stroke lesions will also be collected.

### Data collection

A research assistant will pay regular visits to the hospitals and community-based organisations to screen for potentially eligible participants. The research assistant will contact potential participants by phone and perform a preliminary eligibility assessment. The study aim, intervention, data collection procedure and rights to confidentiality will be explained to eligible patients. Participants’ written informed consent will be obtained before commencing data collection. All consenting participants will be scheduled for baseline (T0) and follow-up assessment (T1, T2 and T3 immediately, 6 months and 12 months post-intervention, respectively). Focus group interviews with the participants in the intervention group (at T1 and T3) and the facilitator (at T1) will be conducted. All interviews will be audio-taped.

### Analyses

Data will be summarised and presented using the appropriate descriptive statistics. The normality of the continuous variables will be assessed using skewness and kurtosis statistics and normal probability plot. The appropriate transformations will be made on the skewed variables before subjecting them to inferential analysis if needed. The homogeneity of the participants’ characteristics between the two study groups will be evaluated by independent t, chi-square or Fisher’s exact tests, as appropriate. The outcome analysis will be performed in accordance with the intention-to-treat principle. The generalised estimating equations models will be used to compare the differential changes in each of the primary and secondary outcomes across time between the two groups. All of the statistical analyses will be performed using SAS release 9.4 (SAS Institute, Cary, NC). All statistical tests involved will be two-sided, with the level of significance set at 0.05. All interview data will be transcribed verbatim. The transcripts will be coded and analysed by two independent researchers. The codes will be grouped to form major themes and sub-themes that correspond to the study aim and objectives.

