### Sample size estimation

The sample size is estimated based on the outcomes of community reintegration, self-efficacy and outcome expectation. In our previous interventional study [23], the effect sizes of a stroke self-management programme on community reintegration, self-efficacy and outcome expectation of performing self-management behaviours were 0.44, 0.55 and 0.53, respectively. Using the power analysis software PASS 16 (NCSS, LLC. Kaysville, Utah, USA), a sample size of 83 participants per study arm is estimated to give this two-arm RCT 80% power at a two-sided 5% level of significance to detect an effect size as small as 0.44 on the primary outcome between the control and intervention groups at a post-intervention time point. Further allowing for a potential attrition rate of up to 20%, 208 participants, with 104 per group, will be recruited.

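### GEE is the stated primary analysis, but without weights or imputation it can bias the T3 effect if dropout depends on earlier scores differently by arm; a likelihood-based repeated-measures model would avoid this under missing at random

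*Protocol article*

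**What the plan says.** The Analyses section states that "The outcome analysis will be performed in accordance with the intention-to-treat principle". It then names the method: "The generalised estimating equations models will be used to compare the differential changes in each of the primary and secondary outcomes across time". No weighting, imputation or working correlation is attached.

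Attrition appears only in Sample size estimation: "Further allowing for a potential attrition rate of up to 20%, 208 participants, with 104 per group, will be recruited".

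Other sections set the context:
- Study design puts T1, T2 and T3 immediately, 6 months and 12 months after the intervention and describes the assessor as blinded.
- Randomisation and blinding says that participants and the facilitator cannot be blinded.
- The primary outcome, the reintegration index, is rated by the participants themselves.
- The hypotheses at the end of the Background claim a benefit at all three post-intervention times, and the Discussion presents the long-term effect as an aim.

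**The concern.** GEE applied to the observed data without weights is guaranteed consistent in general only if dropout does not depend on the outcomes already seen. Inflating the sample for attrition restores precision and leaves any bias in place. Analysing by intention to treat fixes who is counted in which arm. It does not say what is assumed about scores that were never obtained.

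This design makes arm-dependent dropout plausible. One arm is asked to attend eight sessions of 1.5 to 2 hours and the other receives usual care. Participants know which arm they are in. A blinded assessor does not remove that knowledge from a self-rated score.

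T3 closes a long follow-up and carries much of the long-term claim. If low scorers leave one arm more readily than the other, the participants still seen at T3 are no longer a like-for-like comparison.

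**Working it through.** **1. The plan's own figure.** Inputs from Sample size estimation: effect size 0.44, "80% power at a two-sided 5% level of significance", and "a sample size of 83 participants per study arm".
- Normal approximation: n = 2(1.96 + 0.842)² / 0.44² = 81.1, so 82 per arm.
- Exact two-sample t calculation: 82 per arm gives 79.97% power and 83 gives 80.5%, so 83.
- Attrition: 83 / 0.80 = 103.75, so 104 per arm and 208 in total.

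The stated sample size reproduces and is not in question.

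**2. Length of follow-up.** 24 weeks is 24 × 7 / 30.44 = 5.5 months. Adding 12 months puts T3 at about 17.5 months from the start of the intervention.

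**3. Why the working correlation matters.** With a mean for each group at each visit and an independence working correlation, the T3 estimate is the difference between the means of those still observed. If low scorers have left one arm, that arm's mean is too high. A model that uses the correlation between visits draws on the leavers' earlier scores and largely corrects this.

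**4. Simulation.**
- *From the plan:* four visits, true effect 0.44 SD at T1 to T3, and 20% dropout (the planning ceiling, applied in each arm by T3).
- *Assumed, not in the documents:* within-person correlation 0.5 or 0.7, either constant or decaying with time (AR(1)); no return after dropout; log-odds of dropout changing by −0.8 per SD of the last observed score in one arm only; loss per interval 1 − 0.8^(1/3) = 7.2%. Samples were very large, so the figures show bias and not chance.

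T3 estimate (true value 0.44 SD):

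| Method | Low scorers leave intervention arm only | Low scorers leave control arm only |
|---|---|---|
| GEE, independence, constant correlation | 0.52 to 0.55 | 0.33 to 0.36 |
| GEE, independence, decaying correlation | 0.48 to 0.53 | 0.36 to 0.39 |

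For the other methods, across both dropout patterns:
- GEE with exchangeable or unstructured working correlation: within about 0.02 SD of 0.44.
- Likelihood model with the correct covariance: within about 0.005 SD.

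The largest shift is 0.55 − 0.44 = 0.11 SD, a quarter of the planned effect.

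**5. A stronger mechanism.** The log-odds slope is now 1 per SD, either in the control arm only or with opposite signs in the two arms. The bias in the T3 difference in change is:
- independence GEE: −0.06 to −0.27 SD, which is 13% to 61% of 0.44;
- exchangeable GEE: −0.009 to +0.026 SD;
- unstructured GEE: −0.014 to −0.003 SD;
- likelihood model: −0.005 to 0.000 SD.

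**6. When nothing goes wrong.** With completely random dropout, or with the same score-dependent mechanism in both arms, every method is within 0.006 SD of the truth.

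**7. What a shift of this size does.** A bias of −0.10 SD leaves an apparent effect of 0.34, and power at 83 per arm falls from about 80% to about 59%. In the other direction, take the standard error of a difference in change as √(4(1 − r)/83), which is 0.155 at r = 0.5 and 0.120 at r = 0.7. A bias of +0.08 to +0.11 SD then gives a two-sided false-positive rate of 8% (0.08 / 0.155 = 0.5 standard errors) to 15% (0.11 / 0.120 = 0.9). A bias of 0.02 SD gives 5.2% to 5.3%.

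**The case against.** The strongest reply is that the sizeable bias belongs to the independence working correlation, which the plan never specifies. That stands. For a continuous score, GEE with a reasonable working correlation is nearly unbiased in these scenarios. The real contrast is between ignoring and using the within-person correlation, more than between GEE and a mixed model.

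It is also fair that no section says dropout will depend on reintegration or mood or will differ by arm, that 20% is a ceiling, and that the direction of any bias is unknown.

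A reader might infer more than the documents support:
- *That GEE is valid only under completely random dropout.* This is too absolute: the same score-dependent mechanism in both arms cancels almost entirely.
- *That the false-positive rate will be 8% to 15%.* This needs independence GEE, low scorers leaving the intervention arm only, and a bias of 0.08 to 0.11 SD. The mirror case works against the intervention.
- *That the trial is open-label throughout.* The assessor is blinded; participants and facilitator are not.
- *That silence on weights, imputation or sensitivity analyses is itself an error.* A condensed article can leave these to an analysis plan that is not shown, and such a plan could add weights or imputation without contradicting the article.
- *That people who stop attending sessions are lost by design.* Data collection schedules every consenting participant for all assessments.

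What remains is the method the article does name. As stated, whether its T3 result is sound depends on an unstated working correlation and on dropout behaving alike in both arms, and the second cannot be assured in advance.

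**Conclusion.** The concern holds as a risk worth removing, not as a demonstrated error. The intention-to-treat sentence is not wrong, and the sample size is correct. The weakness is that plain GEE is not guaranteed consistent under outcome-dependent dropout, while the only provision for attrition shown concerns power.

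In the main scenarios the T3 effect could be misstated by roughly 0.04 to 0.11 SD in either direction against a planned 0.44. That size needs two conditions together: an independence-type working correlation, and dropout tied to earlier scores differently by arm. It also rests on the assumed correlation, dropout slope and full 20% loss, none of which the documents establish as what will happen. If either condition fails, the bias is about 0.02 SD or less at that dropout slope.

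**What to change.** Make the primary analysis a likelihood-based mixed model for repeated measures on all randomised participants, with REML, unstructured covariance, group-by-visit terms and the baseline score included. Alternatively, keep GEE but weight by the inverse probability of remaining in follow-up, or fit it after multiple imputation done separately by arm.

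Retain plain GEE as a sensitivity analysis and state its working correlation. Add one delta-adjusted analysis that shifts the unobserved scores, because none of these methods covers dropout that depends on the unobserved scores themselves. If the unshown analysis plan already provides this, bring the article's wording into line with it.

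The cost is small: a change of wording, modest extra programming in the SAS release already named, and reliance on a covariance or dropout model. Recruitment stays at 208. The choice should be fixed before any outcome data are seen by arm.

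### The planned GEE contrast is change from baseline, which is less precise than a baseline-adjusted contrast at no saving; the scale of the 0.44 effect size should also be stated

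*Protocol article*

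**What the plan says.** Under Analyses, the protocol article says that GEE models will be "used to compare the differential changes in each of the primary and secondary outcomes across time between the two groups". The Abstract describes the same comparison after listing T0 among the measurement times. The hypotheses at the end of the Background are all worded as improvement relative to baseline, compared with control, at each of the three follow-ups. Taken together, these set the contrast as the between-group difference in change from T0. The article does not list the model terms.

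Under Sample size estimation, "a sample size of 83 participants per study arm" is derived for a target of "80% power at a two-sided 5% level of significance". The stated purpose of that calculation is "to detect an effect size as small as 0.44 on the primary outcome between the control and intervention groups at a post-intervention time point". The 0.44 comes from an earlier study by the same group: "the effect sizes of a stroke self-management programme on community reintegration, self-efficacy and outcome expectation of performing self-management behaviours were 0.44, 0.55 and 0.53". The section does not say whether 0.44 is standardised on the SD of the raw score or of the change score, and it gives no baseline-to-follow-up correlation.

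Under Randomisation and blinding, baseline data are collected before allocation, so a T0 score should exist for everyone randomised.

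**The concern.** The contrast in Analyses and the contrast in Sample size estimation are worded differently and are not linked. One is a difference in change across time; the other is a difference "between the control and intervention groups at a post-intervention time point". These two contrasts have different variances unless the baseline correlation is exactly 0.5.

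A change contrast subtracts the whole of any chance T0 difference between the arms. With equal SDs, the best linear adjustment subtracts only the fraction rho of it. Fixing that coefficient at 1 adds noise whenever rho is below 1. What is at stake is the width of the confidence interval for the RNIL-C comparison and, depending on two quantities that the article does not give, whether the analysis reaches the stated 80% power.

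**Working it through.** **1. The plan's own figure.** Inputs from Sample size estimation: d = 0.44, two-sided alpha 0.05, power 80%, 1:1 allocation, attrition 20%. A two-sample t-test (noncentral t) gives 79.97% power at 82 per arm and 80.45% at 83, so 83 is right. Attrition: 83/0.80 = 103.75, rounded up to 104 per arm, 208 in total. The stated size reproduces exactly.

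**2. What the change contrast estimates.** Take a GEE with T0 as one of the repeated outcomes and terms for group, time and group x time. With complete data, its T1 interaction is the difference in mean change from T0. This was checked on three simulated data sets (83 per arm, exchangeable working correlation, rho 0.3, 0.5 and 0.7). The interaction estimates were 0.4009, 0.4687 and 0.4933, in each case identical to the difference in mean change.

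**3. Variances.** Assume the same SD at T0 and follow-up, taken as 1, and correlation rho between them.
- Raw follow-up score: variance 1.
- Change score: 2(1 - rho).
- Follow-up score adjusted for T0: 1 - rho².
- Adjusted over change: (1 - rho²)/[2(1 - rho)] = (1 + rho)/2, which is below 1 for every rho below 1. It is 0.65 at rho 0.3, 0.75 at 0.5 and 0.85 at 0.7, so the adjusted variance is 35%, 25% and 15% smaller.

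This step does not depend on the scale of 0.44.

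**4. Power if 0.44 is in raw-score SD units (assumption).** The effective effect size is 0.44/sqrt(2(1 - rho)) for change and 0.44/sqrt(1 - rho²) with adjustment. Each goes into the two-sample t power at 83 per arm. The one degree of freedom spent on the T0 slope is ignored.

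| rho | d, change | Power, change | d, adjusted | Power, adjusted |
|---|---|---|---|---|
| 0.3 | 0.372 | 66% | 0.461 | 84% |
| 0.4 | 0.402 | 73% | 0.480 | 87% |
| 0.5 | 0.440 | 80% | 0.508 | 90% |
| 0.6 | 0.492 | 88% | 0.550 | 94% |
| 0.7 | 0.568 | 95% | 0.616 | 98% |

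The change contrast falls below 80% for rho under about 0.49 and exceeds it above that. If all 104 per arm were retained, the threshold would be about 0.36 (normal approximation).

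**5. Power if 0.44 is a change-score effect size.** The change contrast then has 80% power at 83 per arm whatever rho is, and there is no shortfall. The variance ratio in step 3 still applies.

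**The case against.** A reader might infer that power was computed on raw follow-up scores and that the trial is therefore underpowered. The documents do not support that. The sample size section fixes when the comparison is made but not the scale of 0.44, and the source study is not at hand. A shortfall needs both a raw-score effect size and a correlation below about 0.5. No correlation is stated, and at 0.6 or 0.7 the change contrast beats 80%. The 83 per arm also already allows for the full 20% attrition. This part of the objection stands. In the other direction, T3 falls 12 months after a 24-week intervention, about 18 months after T0, so a modest correlation at that visit cannot be ruled out either.

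It can also be said that a journal article need not list model terms and that baseline adjustment is not excluded. That is true. A reader might take the homogeneity tests of characteristics "between the two study groups will be evaluated by independent t, chi-square" or Fisher's exact tests as the only use of baseline, but the article does not say so, and those tests affect neither power nor the primary result. The point therefore rests on the contrast that the article does state. That contrast is change from T0, given consistently in the Abstract, the Background and Analyses, and a more precise alternative uses data already collected.

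Finally, under randomisation the change contrast is unbiased. That stands too: this is a matter of efficiency.

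**Conclusion.** The point holds as an improvement in precision and a clarification. It is not an error of validity or of sample size arithmetic. The stated change contrast has a larger variance than a baseline-adjusted one at every correlation below 1: the adjusted variance is 15% to 35% smaller for rho between 0.7 and 0.3, assuming equal SDs at T0 and follow-up. Whether stated power is also lost cannot be settled from the article. Under a raw-score 0.44, power on change runs from about 66% to 95% over that range of rho; under a change-score 0.44 it is 80% throughout. With adjustment, 83 per arm keeps at least 80% power for any rho of 0 or more if 0.44 is a raw-score effect size. If 0.44 is a change-score effect size, adjusted power is above that of the change contrast for every rho below 1.

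**What to change.** Fit the primary GEE to T1, T2 and T3 with group, time, group x time, the T0 score and T0 x time, and report the adjusted group difference with its confidence interval at each visit. Use the same form for the secondary outcomes.

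This model drops participants who have only T0 data. If they are to be kept, a model with T0 as an outcome and one common T0 mean for both arms is an alternative, but it is not interchangeable with the covariate model. Under an independence working correlation the estimating equations separate by visit, so its T1 contrast is simply the raw follow-up difference (variance 1 in the units above) and T0 contributes no precision. A non-independence structure, for example unstructured, must therefore be specified with it.

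In Sample size estimation, state whether 0.44 is standardised on the raw-score or the change-score SD. If power is to be claimed for the model as fitted, give the assumed baseline correlation as well.

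The cost is a few sentences. There are no new data, the planned software stays, and the number randomised does not change.
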